### Outcomes {12}

In accordance with the Dutch polypectomy guideline, the first surveillance colonoscopy (SC1) is performed 6 months after the resection [13]. The primary outcome is the presence of recurrent adenomatous tissue at the resection site at SC1. Potential recurrence will be assessed by careful optical inspection of the scar, followed by (random) biopsies from each scar quadrant in addition to any areas suspicious for recurrence. The local pathologists will assess the biopsies for microscopic recurrence. Polyp recurrence is defined as histological proof of adenomatous neoplastic tissue in the scar biopsies. Secondary outcomes include technical success and complication rates. Patient and procedural-related characteristics including procedure time, the use of adjunctive resection techniques, and the presence of intra-procedural bleedings are collected.

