### Participant timeline {13}

The participant timeline is shown in Table 2.

**Table 2 Tab2:** SPIRIT schedule of enrolment, interventions, and assessments

	Study period			
	Pre-randomization	Primary study period		Follow-up
	− 14 days	pEMR	STSC	+ 180 days
Enrolment				
Eligibility screening	X	X		
Informed consent	X			
Allocation				
Control		X		
Intervention		X	X	
Assessment				
Baseline variables	X			
Procedural variables		X	X	
Primary outcome				X
Secondary outcomes				X

*pEMR* piecemeal endoscopic mucosal resection, *STSC* soft tip snare coagulation

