### Sample size {14}

In the colorectum, pEMR has been reported to have a recurrence rate of 20% [4]. Based on the findings of Klein et al. and Kandel et al., we anticipate STSC to be able to reduce the number of recurrences by 60 to 8% [7, 14]. For an 80% power with a 2-sided significance level of 5% and an anticipated drop-out rate of 15%, a total of 306 (2 × 153) patients is required for this study.

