### Implementation {16c}

After endoscopic radical polyp removal, the inclusion and exclusion criteria are re-assessed. When study participation requirements are met, a research assistant not involved in the procedure will randomly assign the patient to the intervention or control group during the colonoscopy. Once the patient is allocated to the intervention group, STSC is performed immediately.

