### Statistical methods

#### Statistical methods for primary and secondary outcomes {20a}

The primary outcome will be analyzed according to the intention-to-treat principle with Fisher’s exact test or chi-squared test as appropriate. Recurrences will be reported as recurrence rates (number of cases/total EMRs × 100) for each group. A possible type 1 error will be prevented by including only one lesion per patient. In the unlikely event of a patient having two lesions requiring pEMR and meeting the inclusion/exclusion criteria, only the most distal polyp will be included in the study and the other lesion will be resected during a follow-up colonoscopy. The outcomes of the intention-to-treat analysis will be compared with the per-protocol analysis.

Secondary outcomes include both categorical and continuous variables and will be compared using Student’s *t* test, Wilcoxon rank-sum test, Pearson’s *χ*^2^ test, or Fisher’s exact test as appropriate. For these analyses, a two-tailed *P* < 0.05 will considered to be statistically significant. In case a disbalance exists between potential confounders, multiple regression analysis will be performed for parameters with a *p* ≤ 0.15. Possible risk factors for recurrence will be identified using logistic regression. The Bonferroni correction method will be used to adjust the *p*-value for multiple testing. A cost-effectiveness analysis will be performed in case of superiority of the intervention arm.

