STSC has also been evaluated in observational studies. Kandel et al. observed a recurrence rate of 30% in the control group versus 12% in the STSC group after pEMR [14]. In contrast to the RCT, this study allowed cold avulsion for resecting small residual islands of adenomatous tissue. Limitations of this study however include the absence of performing random biopsies for recurrence assessment and its single tertiary center retrospective design. Sidhu et al. conducted a non-comparative prospective cohort study in six tertiary referral centers in Australia, Canada, and Belgium. Thermal ablation of the resection margin resulted in a recurrence rate of 1.4%. Interestingly, incomplete EMR with STSC and the use of adjunctive treatment resulted in a recurrence rate of 27.1% (13/48), showing a lower prophylactic effect of STSC in EMRs combined with adjunctive therapies [16].

Argon plasma coagulation (APC) is an alternative ablative technique and has also been reported to be effective in preventing recurrence [17–19]. Current evidence is however insufficient to identify which technique is superior.

Potential drawbacks of the RESPECT design are the timing of obtaining informed consent. Patients are eligible once a polyp is not yet removed during the initial colonoscopy but scheduled for a second colonoscopy to perform EMR. This may lead to selection bias since smaller or less challenging polyps might be removed in the same session and therefore will not be included in this study.

In conclusion, the RESPECT study evaluates the effect of STSC in daily practice. By allowing adjunctive techniques, assessing recurrence with focused plus random biopsies, and conducting the EMRs in both expert and non-expert centers, we will evaluate the generalizability of STSC in preventing recurrence.

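### The adjusted analysis chooses its covariates by observed imbalance at p ≤ 0.15, which lets chance pick the model and does not keep out variables that allocation can change

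*Protocol article*

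**What the plan says.** All references are to the protocol article.

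- **Primary analysis.** Statistical methods {20a}: "The primary outcome will be analyzed according to the intention-to-treat principle with Fisher’s exact test or chi-squared test as appropriate". No covariates are involved.
- **Covariate rule.** The next paragraph of {20a}, which opens with the secondary outcomes: "In case a disbalance exists between potential confounders, multiple regression analysis will be performed for parameters with a" p ≤ 0.15. It does not say which test gives the p-value, which variables count as potential confounders, or which outcome is modelled.
- **Variables collected.** Outcomes {12}: "Patient and procedural-related characteristics including procedure time, the use of adjunctive resection techniques, and the presence of intra-procedural bleedings are collected". None of them is labelled a confounder.
- **When they are recorded.** In Table 2, under Participant timeline {13}, the row "Procedural variables" is marked in both the pEMR and the STSC columns.
- **Order of events.** Implementation {16c}: "After endoscopic radical polyp removal, the inclusion and exclusion criteria are re-assessed", then the patient is randomised, and "Once the patient is allocated to the intervention group, STSC is performed immediately".
- **Prognosis.** The Discussion calls adjunctive measures a risk factor for local recurrence.
- **Analysts.** Section {17a} states that data analysts are not blinded.

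**The concern.** Allocation is 1:1, web-based and concealed until eligibility is confirmed, so a between-arm difference in anything fixed before randomisation is chance. A p-value for that difference says nothing about how strongly the variable predicts recurrence, which is what decides whether adjusting for it is useful. The rule can leave out adjunctive technique use, which the protocol itself regards as prognostic, and bring in a weak variable that happens to differ. The model is unknown until unblinded analysts see the data.

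The second problem is that an imbalance screen is most sensitive to variables that treatment really changes. Resection time precedes randomisation, but STSC time follows it. If procedure time is recorded as a total, it may be longer in the STSC arm because of STSC. At equal total time, an STSC patient had a shorter resection than a control patient. If longer resections mark harder lesions, adjusting for total time compares easier STSC cases with harder control cases and favours STSC.

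At stake is the credibility of the adjusted estimate that would be reported beside the primary result.

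**Working it through.** **1. The plan's own figure.** Inputs from Sample size {14}: "In the colorectum, pEMR has been reported to have a recurrence rate of 20"% in controls, 8% with STSC, 80% power, two-sided 5%, 15% drop-out. The pooled-variance two-proportion formula gives 131 per arm; 131/0.85 = 154.1, rounded up to 155, or 310 in total. The stated 306 follows from 130 per arm: 130/0.85 = 152.9, rounded up to 153, and 2 × 153 = 306. Power at 130 per arm is 79.98%. The figure is reproduced to within 4 patients, and 130 evaluable per arm is used below.

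**2. Expected events.** 130 × (0.20 + 0.08) = 36.4, so about 36 recurrences are available to support any model.

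**3. Selection by chance.** For k independent pre-randomisation covariates, P(at least one with p ≤ 0.15) = 1 − 0.85^k.

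| k | P(at least one selected) |
|---|---|
| 1 | 15% |
| 5 | 56% |
| 10 | 80% |

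Some adjusted model is therefore likely, and chance decides its content.

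**4. Selection of total procedure time.** The protocol gives neither the minutes that STSC adds nor the SD of procedure time, so both are assumed. With n per arm, added minutes d and SD s, let z = d / (s√(2/n)). The two-sided critical value at 0.15 is 1.44, and P(selected) ≈ Φ(z − 1.44) + Φ(−z − 1.44). For d = 5, s = 20, n = 153: z = 5/2.287 = 2.19 and P ≈ 77%. The table shows 153 per arm (all randomised) and 130 per arm (evaluable).

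| Added time / SD (min) | 153 per arm | 130 per arm |
|---|---|---|
| 2 / 25 | 25% | 23% |
| 3 / 20 | 45% | 41% |
| 5 / 20 | 77% | 72% |
| 8 / 20 | 98% | 96% |

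**5. Effect on the adjusted estimate when STSC does nothing.** Logistic simulation, 130 per arm, 3,000 trials per scenario. Longer pre-randomisation time is assumed to raise the odds of recurrence by 1.3, 1.5 or 2.0 per SD. Procedure time enters if p ≤ 0.15. False benefit means a significant result in favour of STSC (nominal 2.5%).

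| Added time / SD (min) | STSC odds ratio (1.3 / 1.5 / 2.0) | False benefit (1.3 / 1.5 / 2.0) |
|---|---|---|
| 2 / 25 | 0.98 / 0.98 / 0.96 | 2.4 / 3.1 / 3.0% |
| 3 / 20 | 0.98 / 0.96 / 0.92 | 3.2 / 2.7 / 3.8% |
| 5 / 20 | 0.95 / 0.91 / 0.86 | 4.0 / 4.5 / 6.8% |
| 8 / 20 | 0.91 / 0.85 / 0.76 | 4.9 / 6.6 / 12.9% |

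Without procedure time, the odds ratio stayed at 0.99 to 1.01 and false benefit at 1.8 to 2.8%. If time is unrelated to recurrence (odds ratio 1.0 per SD), the rule produces no bias. The simulation error on a 2.5% rate is √(0.025 × 0.975/3000) ≈ 0.3 percentage points, so the first row is essentially nominal.

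**6. Power.** A separate simulation assumed an odds ratio of 1.7 per SD of lesion size, and adjunctive use in 20% of patients with an odds ratio of 5. At 20% versus 8%, power was 79.9% unadjusted, 80.8% under the p ≤ 0.15 rule limited to baseline variables, and 83.6% with size and adjunctive use always included. Centre was not in that model.

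**The case against.** A reader might infer that the trial is set to declare a false benefit. The documents do not support that, for these reasons.

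- **The confirmatory test is unadjusted.** It is a Fisher's exact or chi-squared test, and the rule sits in the secondary-outcomes paragraph. The type I error of the primary test does not depend on it. This stands, and it limits the severity.
- **Procedure time is never named as a confounder.** It is only listed as collected, the resection part precedes randomisation, and the article does not say when the clock stops. This stands: entry is permitted, not planned. A full covariate list may also sit in an analysis plan that is not shown. However, the article states a selection rule, and a plan that follows it inherits the rule.
- **The p ≤ 0.15 could mean association with the outcome.** The text allows this, although tying the regression to a disbalance makes the between-arm reading more natural. On either reading the data choose the model and post-allocation variables are not barred.
- **The size rests on assumed minutes, SDs and odds ratios.** This stands, and the low end is nominal.
- **The power gain is small.** It is 83.6 − 80.8 = 2.8 points under assumed strong predictors, and planned power rests on the unadjusted test. Power is not the reason to change the rule.

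The cohort result in the Discussion, "the use of adjunctive treatment resulted in a recurrence rate of 27.1% (13/48"), should not be used to size the prognostic effect here. It concerns incomplete EMR in a non-comparative study, and Table 1 excludes macroscopically incomplete resection.

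**Conclusion.** The concern holds as a should-fix on the supportive adjusted analysis. The p ≤ 0.15 screen is a stated rule, so this is more than a missing detail. In a randomised trial it selects on chance, ignores prognostic strength and leaves the model open until the data are seen by unblinded analysts.

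The route through total procedure time is possible but conditional. It needs procedure time to be treated as a confounder, its clock to include the STSC step, STSC to add appreciable time, and longer resections to carry a higher risk of recurrence. If all four hold, the bias favours STSC. Across the scenarios in the table, the adjusted odds ratio under no effect runs from 0.98 to 0.76, and one-directional false benefit from about 2.4% to 12.9% against 2.5%. If any one fails, the bias is negligible or absent. The unadjusted primary test and the sample size of 306 are unaffected.

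**What to change.** 1. Delete the imbalance and p ≤ 0.15 screen from {20a}.
2. Pre-specify one supportive adjusted analysis of the primary outcome: recurrence on arm, lesion size, and adjunctive technique use before randomisation. That last variable needs its time point stated, because Table 2 records procedural variables in the STSC column as well.
3. Account for centre, the stratification factor, economically, for example by conditioning on it or by a random effect. With about 36 expected events and four more centres about to start (Trial status), a fixed term per centre would overload the model, and some centres may have no events.
4. State that variables measured or altered after allocation, including total procedure time and bleeding after randomisation, are not covariates for the STSC effect. They can still be reported by arm.

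The cost is wording only: {12} already collects patient and procedural characteristics, and the sample size does not change. The downside is losing the freedom to add a covariate after seeing an imbalance. The change should be dated before outcome data are analysed.

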### Interim analyses {21b}

We will not perform an interim analysis.

### Methods for additional analyses (e.g., subgroup analyses) {20b}

A sensitivity analysis will compare the histology-proven recurrence rates with the macroscopic recurrence evaluation.

### Methods in analysis to handle protocol non-adherence and any statistical methods to handle missing data {20c}

Missing data will be prevented as much as possible by providing the participating endoscopists with a checklist of the parameters that should be collected during the two colonoscopies. The baseline characteristics are provided by the electronic medical records. The reason for any missing data compromising any outcome will be reported. Depending on the percentage of missing data, parameters with missing data will be imputed or left out of the analysis after consulting a statistical expert.

### Plans to give access to the full protocol, participant-level data, and statistical code {31c}

The full protocol and datasets generated and/or analyzed during the current study are available after publication from the primary investigator on reasonable request.

### Oversight and monitoring

#### Composition of the coordinating center and trial steering committee {5d}

The Radboudumc acts as the coordinating center. The coordinating investigator and the principal investigator together with an expert endoscopist, composing the trial steering committee have monthly meetings to discuss the study progress. The coordinating investigator is responsible for the day-to-day communication with the local principal investigators from the participating centers. Twice a year, members of the Dutch EMR study group are updated on the study’s progress. The coordinating center is responsible for monitoring all participating centers.

### Composition of the data monitoring committee, its role, and reporting structure {21a}

According to the Dutch Federation of Universities (NFU) standard of risk assessment and monitoring, each participating center will be visited by an independent monitor at pre-defined time points. These monitors will assess the adherence to the study protocol and correct handling and storage of study data.

### Adverse event reporting and harms {22}

All adverse events, regardless of a supposed connection to the intervention, will be reported to the study coordinator. In turn, the study coordinator will report adverse events to the Central Committee on Research involving Human Subjects (CCMO) according to Dutch rules and legislation.

### Frequency and plans for auditing trial conduct {23}

Auditing upon invitation of the coordinating hospital board can occur unannounced. The frequency is unknown.

### Plans for communicating important protocol amendments to relevant parties (e.g., trial participants, ethical committees) {25}

Amendments are changes made to the research after a favorable opinion by the accredited medical research ethics committee has been given.

### Dissemination plans {31a}

The trial results will be published open-access. There are no publication restrictions.

## Discussion

The RESPECT study is designed to answer the question of whether STSC after pEMR significantly lowers polyp recurrence rates in daily clinical practice. Although several studies have already investigated STSC performance, some shortcomings have been suggested to impede the generalizability of their findings.

First, only one RCT assessed the effect of STSC on recurrence. This multicenter study included adenomatous polyps ≥ 20 mm removed with complete snare excision, defined as resection of all visible adenomas. As a result, cases in which residual tissue was successfully removed with non-snare adjunctive techniques were excluded [7]. This contrasts with daily clinical practice as adjunctive techniques, such as biopsy forceps and STSC, are regularly used to remove residual tissue. Our study therefore allows the use of adjunctive techniques after pEMR to achieve a macroscopic complete resection of the lesion. Allowing these adjunctive measures, which are a risk factor for local adenomatous tissue recurrence, may reduce STSC performance [15].

Second, the abovementioned RCT was conducted in tertiary centers with highly trained endoscopists and thereby not representing daily practice. The current trial evaluates STSC in both expert and non-expert centers in Germany and the Netherlands.

Third, histological proof of non-recurrence was not always obtained. Biopsies were only taken to confirm areas with suspected recurrences. Recent studies have shown that optical inspection of the post-polypectomy scar may miss residual adenoma in up to 10% [8, 9]. We will therefore assess each scar endoscopically and histologically for recurrent adenoma tissue with random biopsies taken from all four quadrants in addition to any suspicious areas during the surveillance colonoscopy.

STSC has also been evaluated in observational studies. Kandel et al. observed a recurrence rate of 30% in the control group versus 12% in the STSC group after pEMR [14]. In contrast to the RCT, this study allowed cold avulsion for resecting small residual islands of adenomatous tissue. Limitations of this study however include the absence of performing random biopsies for recurrence assessment and its single tertiary center retrospective design. Sidhu et al. conducted a non-comparative prospective cohort study in six tertiary referral centers in Australia, Canada, and Belgium. Thermal ablation of the resection margin resulted in a recurrence rate of 1.4%. Interestingly, incomplete EMR with STSC and the use of adjunctive treatment resulted in a recurrence rate of 27.1% (13/48), showing a lower prophylactic effect of STSC in EMRs combined with adjunctive therapies [16].

Argon plasma coagulation (APC) is an alternative ablative technique and has also been reported to be effective in preventing recurrence [17–19]. Current evidence is however insufficient to identify which technique is superior.

Potential drawbacks of the RESPECT design are the timing of obtaining informed consent. Patients are eligible once a polyp is not yet removed during the initial colonoscopy but scheduled for a second colonoscopy to perform EMR. This may lead to selection bias since smaller or less challenging polyps might be removed in the same session and therefore will not be included in this study.

In conclusion, the RESPECT study evaluates the effect of STSC in daily practice. By allowing adjunctive techniques, assessing recurrence with focused plus random biopsies, and conducting the EMRs in both expert and non-expert centers, we will evaluate the generalizability of STSC in preventing recurrence.

### Trial status

The first patient was randomized on 30 March 2022. To date, 52 patients have been randomized in the participating centers. In the upcoming months, we will start including additional patients in four other centers. Protocol version 7 is being used, and final patient inclusion is expected in April 2025.

## Data Availability

The datasets generated and/or analyzed during the current study are available after publication from the primary investigator (PD) on reasonable request. There are no contractual agreements that limit data access for investigators.

## Abbreviations

CRC: Colorectal carcinoma
LSL: Lateral spreading lesion
EMR: Endoscopic mucosal resection
STSC: Soft tip snare coagulation
RCT: Randomized controlled trial
SPIRIT: Standard Protocol Items: Recommendations for Interventional Trials
pEMR: Piecemeal endoscopic mucosal resection
ASA: American Society of Anesthesiology grade
COAG: Coagulation
SC1: First surveillance colonoscopy
eCRF: Electronic case record form
NFU: Netherlands Federation of University Medical Centres
CCMO: Central Committee on Research involving Human Subjects
APC: Argon plasma coagulation
